## Abstract

**Background:**

Multimorbidity is a common phenomenon among patients treated in general practices. Key challenges within this group include functional difficulties, polypharmacy, treatment burden, fragmentation of care, reduced quality of life and increased health care utilization. These problems cannot be solved in the short consultation time of a general practitioner (GP) since there is an increasing shortage of GPs. In many countries, advanced practice nurses (APNs) are successfully integrated into primary health care for multimorbid patients.

The objective of this study is to examine whether the integration of APNs in the primary care of multimorbid patients in Germany leads to optimized care of the target group and to a reduction in the workload of the GPs.

**Methods:**

The intervention includes the integration of APNs into the care for multimorbid patients in general practice for twelve months. Qualifications for APNs include a master's level academic degree and 500 hours of project-specific training. Their tasks include in-depth assessment, preparation, implementation, monitoring and evaluation of a person-centred and evidence-based care plan.

In this nonrandomized controlled trial, a prospective multicentre mixed methods study will be performed. The main inclusion criterion was the cooccurrence of three chronic diseases. For data collection in the intervention group (*n* = 817), routine data from health insurance companies and association of statutory health insurance physicians (ASHIP) will be used, as well as qualitative interviews. In addition, the intervention will be assessed through documentation of the care process and standardized questionnaires using a longitudinal design. The control group (*n* = 1634) will receive standard care. For the evaluation, routine data from health insurance companies are matched at a ratio of 1:2.

Outcomes will be measured using emergency contacts and GP visits, treatment costs, health status of the patients and the satisfaction of parties involved.

The statistical analyses will include Poisson regression to compare outcomes between the intervention and control groups. Descriptive and analytical statistical methods will be used in the longitudinal analysis of the intervention group data. Cost analysis will compare total costs and subgroup costs between the intervention and control groups. Qualitative data will be analysed using content analysis.

**Discussion:**

Challenges to this protocol could include the political and strategic environment as well as the planned number of participants.

**Trial registration:**

DRKS00026172 on DRKS.

## Administrative information

The structure of this report corresponds to the SPIRIT checklist. Thus, the administrative data are presented first (Table 1).

**Table 1 Tab1:** Administrative information

1Title	** Effects of care of multimorbid patientes in general practices by advanced practice nurses: study protocol for a nonrandomized controlled trial**	
2a and 2b Trial registration	2a: Registry: DRKS00026172 on DRKS (German Clinical Trials Register) 2b: Data Set:	
	**Data category**	**Information**
	Primary registry and trial identifying number	DRKS00026172 on DRKS
	Date of registration in primary registry	2021/09/06
	Secondary identifying numbers	n/a
	Source(s) of monetary or material support	German Innovation Fund of the Federal Joint Committee
	Primary sponsor	German Innovation Fund of the Federal Joint Committee
	Secondary sponsor(s)	n/a
	Contact for public queries	Catholic University of Applied Sciences Mainz [name]. [name] [name] Germany Telephone: [name] [contact]
	Contact for scientific queries	Catholic University of Applied Sciences Mainz [name]. [name] [name] Germany Telephone: [name] [contact]
	Public title	Case-based care of multimorbid patients in general practice by advanced practice nurses (APNs)
	Scientific title	Effects of care of multimorbid patients in general practices by advanced practice nurses (FAMOUS): study protocol for a nonrandomized controlled trial
	Country of recruitment	Germany
	Health condition(s) or problem(s) studied	Multimorbidity
	Intervention(s)	Intervention group: GP-oriented care of multimorbid patients by APNs. Qualification profile of APNs: professional nursing licence, at least 2 years of professional experience in nursing, academic degree at master’s level, 500 hours project-specific advanced training. Task profile: in-depth assessment, preparation, monitoring and evaluation of a person-centred and evidence-based care plan. Control group: multimorbid patients receiving standard care.
	Key inclusion and exclusion criteria	Gender: all genders Minimum age: ≥ 18 years Maximum age: no maximum age Further inclusion criteria: medical diagnosis of at least three chronic diseases, which in the past 12 months in at least three out of four quarters have given rise to general practitioners’ treatment;being in general practitioners’ treatment; insurance with a statutory health insurance company. Exclusion criteria: not fulfilling the inclusion criteria; being in the dying phase according to the assessment of the general practitioner.
	Study type	Interventional, nonrandomized, nonblinded controlled trial
	Date of first enrolment	2021/10/01
	Target sample size	*n*=2451
	Recruitment status	Recruiting
	Primary outcome(s)	Number of emergency contacts
	Key secondary outcomes	Use of other health care facilities (e.g. hospital, nursing home), hospital readmission and visits by general practitioners
3 Protocol version	Issue Date: 2021/10/01	
4 Funding	There was financial support only, provided by the German Innovation Fund of the Federal Joint Committee. The Innovation Fund uses funds from the statutory health insurance (SHI) to support innovative, cross-sectoral new forms of care and patient-oriented care research projects in order to further develop and improve SHI-financed care in Germany	
5a Author details	RS and EG initiated the study design; CDS is responsible for the project management; JK developed the concept of the internal evaluation and will conduct it. EG and MB developed the concept of the external evaluation; BB and MB together with a statistician are planning and will conduct the statistical analysis. BB is responsible for the implementation of the qualitative interviews. All authors contributed to the development and refinement of the study protocol and approved the final manuscript.	
5b Name and contact information for the trial sponsor	Trial Sponsor: Catholic University of Applied Sciences Mainz (CUAS) Contact name: [name]. [name] Address: [name], Germany Telephone: [name] Email: [contact]	
5c Role of funder	This funding source had no role in the design of this study and will not have any role during its execution, analyses, interpretation of the data, or decision to submit results.	

## Introduction

### Background and rationale

Multimorbidity is a common phenomenon among patients in general practices [1, 2]. The term multimorbidity is not well defined. However, most definitions characterize multimorbidity as the cooccurrence of two to three chronic diseases. Because of the somewhat unclear definition, the prevalence rate of multimorbidity in primary care patients varies across studies [2]. One systematic review [2] showed a prevalence of multimorbidity ranging from 12.9% in participants aged 18 years and older to 95.1% in a population aged 65 years and older. Worldwide, more than half of people over the age of 65 years suffer from multiple chronic conditions, most of which are treated in primary care [3]. Multimorbid patients experience many symptoms at the same time. Often, these symptoms cannot be attributed to a causal disease. Therefore, some key problems arise, including functional difficulties, polypharmacy, treatment burden, mental health difficulties, fragmentation of care, reduced quality of life and increased health care utilization [1]. Addressing these challenges requires optimizing functional capacity, rigorous medication management, a greater focus on patient-centred care, and collaboration across health care services [1]. The management of polypharmacy is complex [4], and the implementation of patient-centred care faces several barriers [5]. Thus, these goals can hardly be achieved in the short consultation time a general practitioner (GP) has, which is less than 10 minutes in Germany [6]. In addition, there is an increasing shortage of GPs, especially in rural areas. In Germany, there were already 3,300 unfilled primary care physician positions in 2019, and there will be approximately 11,000 in 2035 [7]. To address this issue, the involvement of other health care professionals is recommended [1]. In many countries, advanced practice nurses (APNs) are successfully integrated into primary health care for multimorbid patients [8, 9]. A systematic review of patient safety, clinical outcomes, cost, and patient satisfaction shows that care offered by nurse practitioners in primary health care settings provides equally good or better outcomes compared with GPs [10]. Outcomes regarding the use of resources, such as the number of emergency visits, hospital admissions, and outpatient contacts, are varied [11]. In addition, findings on the cost effectiveness of integrating APNs in primary care are not very clear. Some studies indicate no increase in costs [11], while other sources have found evidence for cost savings [12].

In Germany, outpatient medical care is predominantly provided by general practitioners. Unlike in many other countries, APNs are not deployed in general practices in Germany. One reason for this is that for a long time, there were no APN education opportunities at the master’s level in Germany. However, academically qualified nurses are now available thanks to the degree programs that have been established in Germany for some time. The objective of this study is to evaluate the care for multimorbid patients by APNs deployed in general practices in rural areas in Germany.

### Explanation for choice of comparators

To evaluate whether the integration of APNs in the primary care setting improves the care of multimorbid patients, a control group from German health care insurance was selected. Persons in the control group are considered to be receiving the current standard care. Therefore, a comparison between the new intervention and standard care is possible. To minimize the risk of confounding variables, participants in the intervention and control groups will be matched for the following variables: (1) age, (2) gender, (3) comorbidity and (4) living in a nursing home.

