### Trial design

The FAMOUS trial is a prospective multicentre mixed methods study. Patients with at least three chronic conditions across nine participating general practices are eligible to be treated as an intervention group by a trained APN. All patients will be treated by APNs for twelve months. Data on the period of intervention are available as data from health insurance companies or the Association of Statutory Health Insurance Physicians (ASHIP) or data collected by the APN. The intervention group will be compared with a control group of patients from German health insurance who are matched according to age, sex, comorbidity and living in a nursing home. The matching will be performed at a ratio of one FAMOUS patient to two control patients.

Qualitative interviews will take place with GPs, APNs and patients to assess factors that are difficult to capture using quantitative data. This evaluation procedure will be carried out by an independent institution (IMBEI). In addition, the intervention will be assessed in more detail in an internal evaluation from the trial sponsor using a longitudinal design.

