## Methods: participants, interventions and outcomes

### Study setting

The study is being conducted in nine general practices in rural areas of Rhineland-Palatinate, Germany. GPs interested in participating in the study were invited to apply and were selected by the project team of Catholic University of Applied Sciences (CUAS). The main criteria for selection were the number of suitable multimorbid patients and the willingness of the practice to implement the intervention. The number of treatment cases in the participating general practices ranges between 2000 and 6000 patients per quarter. Approximately 30% of them are multimorbid. With the size of the practice, we have ensured that the number of potentially eligible patients is sufficient to achieve the number of cases targeted in the study.

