### Eligibility criteria

Patients (or a legal representative) must provide written informed consent before any study procedures occur. The inclusion criteria are as follows: at least 18 years of age; medical diagnosis of at least three chronic diseases that have led to GP treatment in at least three out of four quarters in the last twelve months; and insured by statutory health insurance. The exclusion criterion is a life expectancy less than 12 months as assessed by the treating physician.

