### Recruitment

Recruitment of patients will be carried out by the participating general practitioners through a direct approach. Patients trust their GPs, so a recommendation to participate made by primary care physicians is likely to result in a high participation rate. The recruitment process is supported by the offer of personal contact between APNs and potential participants in the enrolment phase. In addition, to support recruitment, the patients are provided with comprehensive information and educational material about the project in easy-to-understand language, informing them about the project, its objectives and the data collection and processing that will be carried out to achieve the project goals. Posters and flyers are placed in the waiting rooms of the participating GP offices and are customized with the individual data of the general practice and the APN.

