## Methods: data collection, management, analysis

### Data collection methods

For the independent evaluation, data from ASHIP and the health insurance fund will be used for primary and secondary endpoints. To fill in missing data, such as hospital visits for patients with other health insurance, APNs collect health-related data and document patients' emergency and routine visits to any health-related facility (doctor's office, hospital, emergency room). The health insurer provides a data pool for control group matching. All data are transferred to the IMBEI in pseudonymized form. Patients, GPs, and APNs are informed by mailed invitations about the possibility of interview participation and asked to complete a feedback form. Potential interviewees are called via the feedback form, and appointments are made. The qualitative interviews are conducted by telephone using a previously prepared standardized interview guide. There is a separate guide for each interview group, which is finalized after piloting. Interviews are audio recorded and transcribed verbatim.

As part of the internal evaluation, the health status of each participating patient was measured before (t0) and at the end of the patient-individual intervention phase (t1) using the assessment instruments mentioned in the intervention section above as we use the data from these instruments for care and research purposes. Their psychometric data are as follows: DemTect: interrater reliability *r* = 0.993, sensitivity 85.1%, specificity 97% [14]; MNA: internal consistency α = 0.701, test–retest reliability *r* = 0.697 [23]; NRS: with a cut-off point NRS > 4, the sensitivity of ‘unbearable pain’ is 83%, while the specificity is 96.7%, with a cut-off point NRS > 5, the sensitivity is 94%, while the specificity is 85% [24]; PDI: internal consistency α = 0.86, [17]; HAQ: internal consistency α = 0.78–0.98 [25, 26]. The psychometric results of the German translation are as follows: test–retest reliability 0.94, internal consistency α = 0.92, criterion validity 0.76 [27]; MILVA: internal consistency range between α = 0.61–0.94, sensitivity 72%, specificity 59%; [17]. PAINAD-G: internal consistency α = 0.85, interrater stability *r* = 0.80, retest reliability* r* = 0.90 [21]; DEMMI: internal consistency α = 0.83, interrater reliability ICC 0.94 [28].

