### Statistical and further methods

#### Statistical and further methods for primary and secondary outcomes

Statistical analyses of the independent evaluation take place as a comparison between intervention and control groups. Poisson regression will be used for both the primary and secondary endpoints. Adjustments are made for relevant confounders but not for matching variables. APN practices in the intervention group are not considered clusters because a comparable cluster variable is not available for the control group.

Users of the new form of care (patients, participating primary care physicians, and APNs) will be interviewed in qualitative interviews. The interviews will take place at the end of the intervention period to reflect the experiences made. Additionally, primary care physicians will be interviewed at the beginning of the project to map expectations of the new form of care. It can be assumed that a theoretical saturation – i.e., the point at which new interviews no longer provide additional information – will be reached with *n* = 5 GPs and *n* = 5 APNs. Full data collection from all 9 practices participating in the project will nevertheless be targeted. For patients, a number of *n* = 30 participants is expected to reach theoretical saturation.

Cost analysis from the social health insurance perspective will be performed to evaluate potential savings. Costs will be compared between the intervention and the control group. Total cost analysis and cost analysis within subgroups will be carried out to identify areas with the highest costs or cost savings. These subgroups will be identified through the primary and secondary endpoints. Data for the health economic analysis will be obtained from the participating health insurance. Intangible or nonmedical costs will not be analysed since these data are not available in the insurance dataset.

In the internal evaluation, descriptive and analytical statistical methods are used. The patient’s situation at the beginning and at the end of the APN intervention and the nursing process will be described by statistical indicators such as percentual distribution, mean and standard deviation or median and quartile deviation. Depending on the kind of data and on its distribution, parametric or nonparametric statistical analyses will be conducted (e.g., variance analysis, t test, Mann-Whitney U test or Wilcoxon test).

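### Matching omits prior-year emergency contacts and region, and no named covariate or described pre-index data assures adjustment for them in a sample selected by practice, GP and consent

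*Protocol article*

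**What the plan says.** Under Explanation for choice of comparators, the protocol article relies on matching to limit confounding, with participants "matched for the following variables: (1) age, (2) gender, (3) comorbidity and (4) living in a nursing home". Trial design repeats the same four variables and adds: "The matching will be performed at a ratio of one FAMOUS patient to two control patients". The source of controls is given under Data collection methods: "The health insurer provides a data pool for control group matching". No regional limit on that pool is stated.

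The intervention group is reached differently. The practices are nine, all in rural Rhineland-Palatinate. They applied to take part and were then chosen by the project team: "The main criteria for selection were the number of suitable multimorbid patients and the willingness of the practice to implement the intervention". For patients, "Recruitment of patients will be carried out by the participating general practitioners through a direct approach", and written consent is required. Under Eligibility criteria the treating physician also excludes patients judged to have less than 12 months to live.

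On the analysis, "Poisson regression will be used for both the primary and secondary endpoints", and "Adjustments are made for relevant confounders but not for matching variables". The confounders are not listed. The same section says practices are not treated as clusters because controls have no comparable variable. The initial data listed under Participant timeline are age, sex, diagnoses, and number and duration of illnesses. Trial design describes data for the intervention period only.

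**The concern.** In a nonrandomized comparison, any difference in underlying contact rate between the arms that is neither matched nor adjusted for passes directly into the primary rate ratio. The endpoint counts on-call visits, GP contacts outside office hours and unplanned admissions. A patient's own recent use of these services, and local access to them, are plausible determinants of that count. Two patients of the same age, sex, comorbidity and residence type can differ widely on both.

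The arms also pass through different filters. Practice willingness, the GP's approach, consent and the GP's judgement of life expectancy apply to the intervention group, and none has a stated counterpart in the insurer's pool. If GPs tend to approach heavy users, a real benefit could be hidden. If consent and the life-expectancy exclusion favour stable patients, a benefit could be mimicked. At stake is whether the primary rate ratio can be attributed to advanced practice nurse care.

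**Working it through.** **Inputs from Sample size.** Control rate 2.7 and target rate 2.295 contacts per patient-year (ratio 0.85); alpha 0.05, taken here as two-sided because sidedness is not stated; power 80%; dropout 30%; 817 intervention and 1634 control patients. The size of the cluster effect is not stated.

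**The plan's own figure.** For a Wald test on the log rate ratio at 1:2:

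n = (1.960 + 0.842)² × (1/2.295 + 1/(2 × 2.7)) / (ln 0.85)² ≈ 185 intervention patients, or 185/0.7 ≈ 264 after dropout.

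Reaching 817 requires 817 × 0.7 = 572 analysed patients, a design effect of about 572/185 ≈ 3.1. With about 64 analysed patients per practice, that is an intracluster correlation of about (3.1 − 1)/(64 − 1) ≈ 0.03. This is plausible, so 817 is neither confirmed nor refuted, and the point does not depend on it.

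**Step 1: standard error of the analysis as described.** Unclustered Poisson, no true effect, 30% dropout applied to both arms (572 and 1144 analysed):

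SE = √[1/(572 × 2.7) + 1/(1144 × 2.7)] = 0.0312.

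**Step 2: chance of a significant result from baseline imbalance alone.** The imbalances are assumptions; the document gives none.

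- 5%: ln 1.05 / 0.0312 ≈ 1.57, so Φ(1.57 − 1.96) ≈ 0.35.
- 10%: ln 1.10 / 0.0312 ≈ 3.06, so Φ(3.06 − 1.96) ≈ 0.86.

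**Step 3: a larger standard error.** If the cluster allowance in the sample size carried through to the analysis, 80% power at 0.85 implies SE = |ln 0.85| / (1.960 + 0.842) = 0.1625/2.802 ≈ 0.058. The chance of significance in favour of the intervention, with no true effect, is then:

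| Residual bias (rate ratio) | SE 0.058 |
|---|---|
| 0.95 | Φ(0.0513/0.058 − 1.96) ≈ 0.14 |
| 0.90 | Φ(0.1054/0.058 − 1.96) ≈ 0.44 |

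The nominal rate in that direction is 0.025. For the same two biases, the unclustered analysis gives about 0.37 and 0.90. These differ slightly from Step 2 because a ratio of 0.95 or 0.90 lies further from 1 on the log scale than 1.05 or 1.10, and because the lower intervention rate enters the standard error.

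**Step 4: how much imbalance would match the target effect?** Take one binary trait, high prior emergency use, that multiplies the later rate by R, with prevalence p₁ in the intervention group and p₀ in controls. The bias is [1 + p₁(R − 1)] / [1 + p₀(R − 1)]. R and both prevalences are assumed. With p₀ = 30%:

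| R | p₁ giving a spurious 0.85 |
|---|---|
| 2 | 10.5% |
| 3 | 18% (1.36/1.60 = 0.85) |
| 4 | 20.5% |

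In the other direction, at R = 3, p₁ of about 44% gives 1.88/1.60 ≈ 1.18, which would fully hide a true 15% reduction.

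**The case against.** The strongest reply is that the primary model already provides for adjustment beyond the four matching variables, and that Additional analyses foresees subgroup and sensitivity analyses. An article may leave the covariate list to an analysis plan that is not shown. This reply stands to the extent that a reader who infers that prior use and region are left uncontrolled goes further than the text allows. Either could be among the intended confounders. It does not dispose of the point. An analysis plan can adjust only for data that were requested, and the article describes neither a pre-intervention extract nor prior contacts among the initial data. Restricting the control pool by region is a design step.

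Other inferences also go too far. The article does not say that GPs hand-pick patients: it describes a direct approach, supported by posters and flyers, with eligible patients informed by their GP. It does not say that the control pool is nationwide; its scope is simply not stated. Nor does it show that a complete baseline year is already held. The criterion under Eligibility criteria implies some look-back over the preceding year, but on diagnoses and GP treatment, not on admissions or emergency use.

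Finally, matching on a prior-year outcome can itself introduce regression to the mean when the groups come from different populations, and the trial openly declares itself nonrandomized. Both are fair. They favour covariate adjustment and a visible baseline comparison over matching alone, and they mean that the remedy reduces selection without removing it.

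**Conclusion.** The point holds in a limited form. The matching set omits prior-year emergency contacts and region or rurality, no adjustment variable is named, and no pre-index data period is described. These factors are therefore unmatched and not assured of adjustment in a sample selected by practice, GP and consent.

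Assumed imbalances of 5% and 10% with no true effect give significance with probability about 35% and 86% under the unclustered Poisson standard error. Under the standard error implied by the design power, biases of 0.95 and 0.90 give about 14% and 44% in favour of the intervention. All these figures rest on assumed imbalances, two-sided testing and, for the first pair, no overdispersion. They show that confounding could reach the size of the 15% target. They do not show that it will, and the document does not fix its direction.

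**What to change.** - Request routine data for the 12 months before the index date for both arms.
- Prespecify prior-year emergency contacts as a covariate in the primary model, and add them to the matching where they are complete. Use on-call and out-of-hours contacts for all patients, and unplanned admissions for those insured by the participating insurer. Add a sensitivity analysis limited to the latter.
- Draw controls from comparable rural districts and exclude patients of the nine practices.
- Report baseline-year contact rates by arm as the check on comparability.

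The cost is one more year of data and somewhat fewer close matches. Prior inpatient data will be missing for patients of other insurers, because the article describes no collection of their admissions before enrolment. Selection by consent and GP judgement is reduced but not removed.
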